**Supplementary Data Figure 1. Correlation between kidney fibrosis and biomarker levels.**

Scatter plots showing the association between kidney interstitium fibrosis score (x-axis) and log2-transformed gene expression levels (transcript per million, TPM, n = 474) of nine biomarkers (y-axis). Each panel displays the Pearson correlation coefficient (R) and corresponding two-sided P-value. Solid lines represent fitted values from linear regression models, and shaded areas indicate 95% confidence intervals.

[figure not shown]

**Supplementary Figure 2. Forest plots of hazard ratios and time-dependent AUC across subgroups in *APOL1* high-risk individuals.**

(Right panel) Forest plot showing hazard ratios for the composite outcome in different subgroups. Points indicate hazard ratio estimates, horizontal lines represent 95% confidence intervals, and shaded density curves represent the distribution of hazard ratio estimates. The vertical dashed line corresponds to a hazard ratio of 1. (Left panel) Similar plots for the time-dependent AUC with 95% confidence intervals. DM, diabetes mellitus; HTN, hypertension. G1 and G2 denote eGFR categories (G1: eGFR ≥90; G2: 60–89 mL/min/1.73 m^2). A1 denotes UACR categories (A1: <30 mg/g). Combined labels represent joint eGFR and UACR strata, and suffixes non-DM (nDM), non-HTN (nHTN); nKD excludes any history of kidney disease, including hematuria or ureteral disorders.

[figure not shown]

**Supplementary Figure 3. Forest plots of hazard ratios and time-averaged AUC across subgroups in *APOL1* low-risk individuals.**

(Right panel) Forest plot showing hazard ratios for the composite outcome in different subgroups. Points indicate hazard ratio estimates, horizontal lines represent 95% confidence intervals, and shaded density curves represent the distribution of hazard ratio estimates. The vertical dashed line corresponds to a hazard ratio of 1. (Left panel) Similar plots for the time-dependent AUC with 95% confidence intervals. DM, diabetes mellitus; HTN, hypertension. G1 and G2 denote eGFR categories (G1: eGFR ≥90; G2: 60–89 mL/min/1.73 m^2). A1 denotes UACR categories (A1: <30 mg/g). Combined labels represent joint eGFR and UACR strata, and suffixes non-DM (nDM), non-HTN (nHTN); nKD excludes any history of kidney disease, including hematuria or ureteral disorders.

**Supplementary Table 1. Baseline characteristics of the training and testing cohort**

|  |                                     | APOLI high risk with eGFR $\geq 60$ ml/min/1.73m  |                    |      |
|--|-------------------------------------|----------------------------------------------------------------------|--------------------|------|
|  |                                     | Training                                                             | Testing            | P    |
|  | Number                              | 680                                                                  | 171                |      |
|  | Age - yr                            | 49.38 $\pm$ 15.07                                                    | 48.58 $\pm$ 15.1   | 0.54 |
|  | Female - no. (%)                    | 452(66.47%)                                                          | 114(66.67%)        |      |
|  | SBP - mmHg                          | 128.61 $\pm$ 17.73                                                   | 128.27 $\pm$ 18.09 | 0.82 |
|  | DBP- mmHg                           | 77.66 $\pm$ 11.76                                                    | 77.32 $\pm$ 12.47  | 0.74 |
|  | Body Mass Index - kg/m  | 32.2 $\pm$ 7.69                                                      | 32.54 $\pm$ 8.44   | 0.61 |
|  | Hemoglobin A1c (%)                  | 6.57 $\pm$ 1.87                                                      | 6.56 $\pm$ 1.62    | 0.97 |
|  | Creatinine (mg/dL)                  | 0.88 $\pm$ 0.21                                                      | 0.87 $\pm$ 0.22    | 0.92 |
|  | Blood Urea Nitrogen (mg/dL)         | 12.99 $\pm$ 4.87                                                     | 13.25 $\pm$ 5.44   | 0.55 |
|  | eGFR - ml/min/1.73m     | 90.73 $\pm$ 16.94                                                    | 90.03 $\pm$ 17.47  | 0.63 |
|  | UACR (IQR) - mg/g                   | 17.23(11-31)                                                         | 17.23(11-31)       | 0.67 |
|  | 30~299 - no. (%)                    | 88(12.94)                                                            | 24(14.03)          |      |
|  | $\geq 300$ - no. (%)                | 20(2.94)                                                             | 5(2.92)            |      |
|  | Diagnostic group - no. (%)          |                                                                      |                    |      |
|  | Hypertension                        | 425(62.5)                                                            | 106(61.99)         | 0.9  |
|  | Diabetes Mellitus                   | 186(27.3)                                                            | 51(29.8)           | 0.52 |
|  | Cardiovascular Disease              | 64(9.41)                                                             | 14(8.19)           | 0.62 |
|  | p.N264K                             | 35(5.15)                                                             | 5(2.92)            | 0.22 |
|  | Event - no. (%)                     |                                                                      |                    |      |
|  | Composite Event                     | 121(17.79)                                                           | 32(18.71)          | 0.78 |
|  | Deceased                            | 48(7.06)                                                             | 14(8.19)           | 0.61 |
|  | Kidney event                        | 96(14.12)                                                            | 24(14.04)          | 0.98 |
|  | $\geq 40$ % eGFR decline            | 89(13.09)                                                            | 21(12.28)          | 0.78 |
|  | Kidney transplantation              | 7(1.03)                                                              | 3(1.75)            | 0.43 |
|  | End-stage kidney disease            | 23(3.38)                                                             | 3(1.75)            | 0.27 |
|  | Dialysis                            | 12(1.76)                                                             | 3(1.75)            | 0.99 |
|  | Follow-up time - yr                 | 7.12 $\pm$ 2.91                                                      | 7.43 $\pm$ 2.78    | 0.21 |
|  | Time to event - yr                  | 6.46 $\pm$ 3.1                                                       | 6.72 $\pm$ 2.92    | 0.32 |

UACR: urine albumin-to-creatinine ratio; SBP: systolic blood pressure; DBP: diastolic blood pressure; eGFR: estimated glomerular filtration rate.

**Supplementary Table 2. Comparison of Protein Hazard Ratios Between CRIC and PMBB Cohorts and Overlap**

| id            | Target    | Hazard Ratios per log2 (95%CI) adjusted for eGFR |                             |                  |                  | Include in APRS |
|---------------|-----------|--------------------------------------------------|-----------------------------|------------------|------------------|-----------------|
|               |           | CRIC (N. 65)
eGFR<60                          | PMBB APOL1 high-risk |                  |                  |                 |
|               |           |                                                  | all                         | eGFR≥60          | eGFR<60          |                 |
| seq.11388.75  | WFDC2     | 3.54 (2.98,4.22)                                 | 3.39(2.79-4.13)             | 3.73(2.89-4.81)  | 2.77(2.06-3.72)  | Yes             |
| seq.2789.26   | MMP7      | 1.1 (1.06,1.14)                                  | 1.69(1.47-1.93)             | 1.86(1.51-2.30)  | 1.51(1.27-1.80)  | Yes             |
| seq.8841.65   | CILP2     | 0.57 (0.5,0.64)                                  | 0.47(0.40-0.55)             | 0.41(0.33-0.52)  | 0.53(0.42-0.66)  | Yes             |
| seq.4297.62   | SPON1     |                                                  | 4.60(3.54-5.97)             | 4.87(3.43-6.92)  | 4.13(2.80-6.11)  | Yes             |
| seq.4920.10   | LYZ       |                                                  | 3.98(3.20-4.95)             | 4.28(3.22-5.68)  | 3.22(2.27-4.57)  | Yes             |
| seq.19555.1   | SUMO2     |                                                  | 2.85(2.42-3.36)             | 3.03(2.44-3.78)  | 2.43(1.90-3.11)  | Yes             |
| seq.6036.78   | EPHA10    |                                                  | 2.68(2.26-3.19)             | 2.85(2.26-3.61)  | 2.27(1.76-2.93)  | Yes             |
| seq.15304.1   | REG3A     |                                                  | 2.13(1.88-2.42)             | 2.36(1.99-2.81)  | 1.80(1.50-2.18)  | Yes             |
| seq.7655.11   | NPPB      |                                                  | 1.47(1.37-1.58)             | 1.68(1.52-1.86)  | 1.29(1.17-1.42)  | Yes             |
| seq.9234.8    | TWSG1     | 4.95 (3.87,6.32)                                 | 9.22(6.31-13.46)            | 8.77(5.15-14.93) | 8.46(4.74-15.1)  |                 |
| seq.15453.3   | AMBP      | 4.55 (3.61,5.74)                                 | 8.13(5.38-12.29)            | 7.87(4.29-14.43) | 6.59(3.68-11.79) |                 |
| seq.6245.4    | NECTIN2   | 4.46 (3.51,5.66)                                 | 3.63(2.41-5.46)             | 1.81(0.90-3.64)  | 4.35(2.44-7.74)  |                 |
| seq.3438.10   | FSTL3     | 4.26 (3.38,5.36)                                 | 3.89(3.10-4.86)             | 3.97(2.90-5.43)  | 3.42(2.43-4.81)  |                 |
| seq.15472.16  | LRP11     | 4.15 (3.32,5.18)                                 | 4.22(3.13-5.69)             | 4.21(2.70-6.55)  | 3.59(2.36-5.44)  |                 |
| seq.8005.1    | MXRA7     | 3.45 (2.93,4.07)                                 | 2.99(2.33-3.85)             | 3.11(2.10-4.61)  | 2.62(1.86-3.68)  |                 |
| seq.5349.69   | DLL1      | 3.37 (2.70,4.21)                                 | 3.64(2.73-4.85)             | 3.77(2.51-5.66)  | 3.16(2.09-4.78)  |                 |
| seq.19575.4   | EPOR      | 3.24 (2.77,3.77)                                 | 3.57(2.59-4.91)             | 3.68(2.28-5.94)  | 3.26(2.10-5.06)  |                 |
| seq.19130.81  | SERPINB8  | 3.19 (2.68,3.80)                                 | 2.71(2.17-3.39)             | 2.57(1.86-3.53)  | 2.62(1.89-3.62)  |                 |
| seq.8587.21   | SPINK14   | 3.06 (2.57,3.63)                                 | 2.53(1.82-3.51)             | 2.13(1.23-3.71)  | 2.34(1.53-3.58)  |                 |
| seq.9468.8    | LMAN2     | 2.92 (2.38,3.58)                                 | 5.81(4.39-7.69)             | 8.78(5.93-13.02) | 3.76(2.57-5.49)  |                 |
| seq.8480.29   | EFEMP1    | 2.88 (2.37,3.49)                                 | 3.56(2.81-4.51)             | 4.81(3.49-6.63)  | 2.48(1.76-3.48)  |                 |
| seq.5452.71   | ASGR1     | 2.84 (2.41,3.36)                                 | 1.99(1.60-2.46)             | 1.66(1.15-2.42)  | 1.9(1.44-2.5)    |                 |
| seq.15585.304 | FBLN5     | 2.82 (2.30,3.46)                                 | 1.69(1.36-2.11)             | 1.90(1.41-2.57)  | 1.44(1.04-1.99)  |                 |
| seq.14136.234 | CD93      | 2.78 (2.24,3.45)                                 | 3.72(2.81-4.93)             | 3.83(2.56-5.73)  | 3.17(2.13-4.71)  |                 |
| seq.3738.54   | CSF1      | 2.66 (2.25,3.15)                                 | 1.75(1.28-2.39)             | 2.05(1.33-3.16)  | 1.51(0.96-2.38)  |                 |
| seq.2997.8    | JAM2      | 2.65 (2.15,3.28)                                 | 5.27(3.75-7.40)             | 6.32(3.61-11.05) | 4.03(2.59-6.28)  |                 |
| seq.9316.67   | WFDC1     | 2.54 (2.14,3.02)                                 | 3.27(2.65-4.03)             | 3.75(2.76-5.08)  | 2.63(1.97-3.53)  |                 |
| seq.2944.66   | NBL1      | 2.52 (2.24,2.84)                                 | 3.62(2.81-4.67)             | 4.36(3.01-6.32)  | 2.97(2.11-4.19)  |                 |
| seq.12488.9   | MCTS1     | 2.49 (2.18,2.84)                                 | 1.90(1.61-2.24)             | 1.83(1.42-2.37)  | 1.77(1.43-2.2)   |                 |
| seq.15640.54  | TAGLN     | 2.37 (2.02,2.79)                                 | 2.84(2.43-3.31)             | 3.16(2.58-3.86)  | 2.36(1.86-2.98)  |                 |
| seq.9021.1    | HAVCR1    | 2.31 (2.15,2.48)                                 | 1.61(1.43-1.81)             | 1.93(1.63-2.30)  | 1.40(1.20-1.64)  |                 |
| seq.12008.3   | CD7       | 2.24 (1.96,2.56)                                 | 1.95(1.61-2.36)             | 1.61(1.19-2.16)  | 1.99(1.52-2.61)  |                 |
| seq.2774.10   | IL16      | 2.16 (1.83,2.56)                                 | 2.10(1.67-2.65)             | 1.60(1.15-2.23)  | 2.41(1.73-3.34)  |                 |
| seq.14615.46  | KRTAP2-4  | 1.91 (1.65,2.20)                                 | 1.78(1.38-2.30)             | 1.28(0.89-1.85)  | 2.09(1.46-2.98)  |                 |
| seq.16322.10  | MZB1      | 1.86 (1.67,2.08)                                 | 1.96(1.63-2.37)             | 2.35(1.76-3.13)  | 1.57(1.22-2.01)  |                 |
| seq.2765.4    | GDF11     | 1.85 (1.61,2.11)                                 | 0.90(0.70-1.15)             | 0.85(0.61-1.20)  | 1.01(0.71-1.45)  |                 |
| seq.18841.1   | SERPINB13 | 1.83 (1.62,2.06)                                 | 1.23(1.03-1.48)             | 1.05(0.80-1.36)  | 1.30(1.01-1.67)  |                 |
| seq.7970.315  | ART3      | 1.63 (1.45,1.84)                                 | 1.92(1.58-2.33)             | 1.63(1.19-2.22)  | 1.95(1.52-2.51)  |                 |
| seq.4493.92   | IL11      | 1.56 (1.24,1.97)                                 | 1.41(0.94-2.10)             | 1.84(1.05-3.22)  | 1.30(0.72-2.32)  |                 |
| seq.5954.62   | PTH       | 1.48 (1.36,1.61)                                 | 1.84(1.60-2.13)             | 1.90(1.52-2.38)  | 1.68(1.40-2.03)  |                 |
| seq.6247.9    | SIRPB1    | 1.43 (1.31,1.55)                                 | 1.92(1.63-2.28)             | 1.74(1.34-2.25)  | 1.86(1.49-2.34)  |                 |
| seq.8219.14   | ZG16      | 1.32 (1.21,1.43)                                 | 1.02(0.99-1.06)             | 1.01(0.96-1.07)  | 1.02(0.97-1.08)  |                 |
| seq.5852.6    | S100A12   | 1.29 (1.18,1.40)                                 | 1.44(1.24-1.68)             | 1.57(1.28-1.93)  | 1.42(1.14-1.77)  |                 |
| seq.14175.78  | SCP2D1    | 1.27 (1.19,1.35)                                 | 1.53(1.34-1.75)             | 1.73(1.40-2.14)  | 1.29(1.08-1.54)  |                 |
| seq.7245.2    | CELF2     | 1.21 (1.05,1.39)                                 | 1.12(0.98-1.28)             | 1.22(1.02-1.47)  | 1.09(0.90-1.32)  |                 |
| seq.5090.49   | LILRB1    | 0.91 (0.88,0.95)                                 | 1.00(0.9-1.12)              | 1.00(0.86-1.17)  | 1.00(0.86-1.16)  |                 |
| seq.4914.10   | CGA       | 0.83 (0.79,0.87)                                 | 0.91(0.85-0.97)             | 0.94(0.85-1.03)  | 0.88(0.80-0.96)  |                 |
| seq.9322.15   | RCN1      | 0.82 (0.75,0.89)                                 | 0.90(0.81-1.00)             | 0.91(0.79-1.05)  | 0.92(0.79-1.07)  |                 |
| seq.11377.19  | ADH7      | 0.81 (0.71,0.92)                                 | 0.70(0.55-0.89)             | 0.73(0.52-1.03)  | 0.70(0.49-0.98)  |                 |
| seq.18179.56  | SMS       | 0.8 (0.58,1.10)                                  | 0.38(0.21-0.69)             | 0.38(0.17-0.88)  | 0.32(0.13-0.78)  |                 |
| seq.9185.15   | TFF1      | 0.77 (0.71,0.82)                                 | 0.93(0.82-1.06)             | 0.98(0.82-1.19)  | 0.95(0.80-1.13)  |                 |
| seq.9416.77   | CPM       | 0.77 (0.68,0.87)                                 | 0.92(0.67-1.26)             | 0.88(0.57-1.34)  | 1.02(0.63-1.65)  |                 |

|               |           |                  |                 |                 |                 |  |
|---------------|-----------|------------------|-----------------|-----------------|-----------------|--|
| seq.12630.8   | ARFIP2    | 0.75 (0.66,0.86) | 1.08(0.83-1.41) | 0.82(0.57-1.18) | 1.50(1.01-2.23) |  |
| seq.5632.6    | CRTAC1    | 0.73 (0.66,0.81) | 0.96(0.76-1.21) | 0.99(0.70-1.39) | 1.01(0.72-1.40) |  |
| seq.5491.12   | SPOCK2    | 0.72 (0.62,0.85) | 0.62(0.50-0.77) | 0.79(0.58-1.07) | 0.55(0.40-0.77) |  |
| seq.2961.1    | PROC      | 0.68 (0.56,0.82) | 0.26(0.18-0.37) | 0.26(0.16-0.42) | 0.28(0.16-0.50) |  |
| seq.10521.10  | MXRA8     | 0.67 (0.55,0.81) | 1.92(1.39-2.65) | 1.37(0.83-2.25) | 2.23(1.47-3.38) |  |
| seq.18274.2   | SERF2     | 0.64 (0.49,0.83) | 0.19(0.11-0.33) | 0.11(0.05-0.27) | 0.26(0.12-0.55) |  |
| seq.14133.93  | IL1R2     | 0.62 (0.53,0.73) | 0.65(0.49-0.86) | 0.74(0.50-1.09) | 0.62(0.41-0.94) |  |
| seq.10833.64  | HHIP      | 0.61 (0.50,0.74) | 1.00(0.73-1.35) | 1.03(0.67-1.59) | 1.08(0.70-1.65) |  |
| seq.5091.28   | LILRB2    | 0.60 (0.51,0.71) | 1.37(0.95-1.96) | 1.77(1.07-2.94) | 1.15(0.69-1.92) |  |
| seq.17495.141 | SIRT3     | 0.59 (0.49,0.73) | 0.54(0.43-0.69) | 0.55(0.39-0.75) | 0.53(0.37-0.77) |  |
| seq.2706.69   | SERPINA7  | 0.58 (0.45,0.76) | 0.41(0.26-0.63) | 0.44(0.23-0.81) | 0.37(0.20-0.68) |  |
| seq.9583.17   | RNF24     | 0.53 (0.41,0.67) | 0.65(0.43-0.99) | 0.47(0.26-0.85) | 0.79(0.44-1.43) |  |
| seq.5107.7    | NOTCH1    | 0.53 (0.37,0.74) | 0.57(0.32-1.03) | 0.40(0.17-0.92) | 0.78(0.34-1.76) |  |
| seq.19584.33  | FGF9      | 0.50 (0.38,0.67) | 0.26(0.17-0.40) | 0.31(0.18-0.56) | 0.26(0.13-0.51) |  |
| seq.13554.78  | REPIN1    | 0.49 (0.33,0.73) | 0.33(0.18-0.58) | 0.28(0.12-0.68) | 0.36(0.16-0.78) |  |
| seq.18896.23  | HS6ST3    | 0.46 (0.36,0.60) | 0.71(0.47-1.07) | 0.59(0.33-1.06) | 0.88(0.49-1.58) |  |
| seq.5735.54   | C1GALT1C1 | 0.45 (0.37,0.54) | 0.18(0.10-0.34) | 0.14(0.06-0.34) | 0.30(0.12-0.75) |  |
| seq.18380.78  | ALB       | 0.40 (0.33,0.49) | 2.04(1.26-3.30) | 2.92(1.42-6.00) | 1.41(0.74-2.69) |  |
| seq.5359.65   | PIM1      | 0.27 (0.20,0.37) | 0.38(0.22-0.65) | 0.51(0.25-1.04) | 0.31(0.14-0.69) |  |

## Summary of the change

This revised protocol expands and refines our original design to improve risk prediction for APOL1-associated kidney disease. We now leverage multiple large cohorts (Penn Medicine BioBank, ARIC, UK Biobank) to increase sample size and diversity. Our focus is narrowed to individuals of African ancestry with APOL1 high-risk genotypes (two risk alleles) and preserved kidney function ( $\text{eGFR} \geq 60 \text{ mL/min/1.73m}^2$  without significant albuminuria) at baseline, targeting the pre-chronic kidney disease phase.

## 1. Background

Chronic kidney disease (CKD) affects over 850 million people worldwide and over 800,000 in the U.S., imposing substantial morbidity, mortality, and health-care costs. Individuals of African ancestry suffer a disproportionately high ESKD burden, driven in part by APOL1 high-risk genotypes (two risk alleles, G1 and/or G2). An estimated 4–5 million Black Americans (and tens of millions globally) carry APOL1 high-risk genotypes, which confer ~5-fold higher risk of kidney failure. However, most APOL1–high-risk carriers remain healthy; only ~20% progress to kidney failure. Emerging APOL1-targeted therapies (e.g., inaxaplin) offer promise for prevention, but their utility depends on identifying those high-risk carriers likely to progress before CKD develops. Currently, clinical risk equations (such as the Kidney Failure Risk Equation [KFRE]) perform poorly when eGFR is preserved. Broad plasma proteomic profiling can capture subclinical renal injury and dynamic biology that genomic or creatinine-based measures may miss. In our preliminary analyses, multiple circulating protein biomarkers were associated with long-term kidney outcomes in APOL1–high-risk individuals. We now propose to refine and validate APOL1 Proteomic Risk Score (APRS) for early risk stratification in this population.

## 2. Objectives

The primary and secondary objectives are to:

- Develop and validate a plasma APOL1 proteomic risk score (APRS) for prediction of a composite kidney outcome ( $\geq 40\%$  decline in eGFR, initiation of dialysis or kidney transplantation, or all-cause death) in APOL1 high-risk individuals with preserved kidney function.

- Compare APRS performance (discrimination) to standard models including the KFRE, APOL1 genotype status, and CKD polygenic risk scores.

- Externally validate APRS in independent, ancestry-matched cohorts (ARIC and UK Biobank) using harmonized outcomes.

- Assess biological plausibility by evaluating the association of APRS protein components with kidney tissue pathology (e.g., interstitial fibrosis).

### 3. Methods

#### 3.1 Study Design and Setting

This is a retrospective cohort study of adult participants with APOL1 high-risk genotypes drawn from the Penn Medicine BioBank (PMBB) and two external cohorts (ARIC, UK Biobank). The primary analysis will focus on APOL1-high-risk individuals of African ancestry with baseline eGFR >60 mL/min/1.73m^2 (preserved kidney function). The APRS will be derived in the PMBB cohort and validated in ARIC (African-American participants) and UK Biobank (African descent participants). All proteomic assays and outcome ascertainment will be harmonized across cohorts.

#### 3.2 Penn Medicine BioBank (Primary Cohort)

PMBB is an EHR-linked biobank at the University of Pennsylvania with >40,000 participants, ~30% non-European ancestry. We will identify all African-American PMBB participants with APOL1 high-risk genotype (two risk alleles: G1/G1, G2/G2, or G1/G2), age ≥18, and baseline eGFR >60 mL/min/1.73m^2. APOL1 genotype was determined via whole-exome sequencing (Regeneron) or equivalent genotyping. Plasma proteomic profiles (7,549 proteins) were measured at baseline using the SomaScan aptamer platform. We have identified 1,113 eligible participants for the primary cohort (expanded from 550 in the prior dataset). Additional CKD participants with APOL1 high-risk genotype and 967 African ancestry APOL1 low-risk participants (267 newly added) and 698 European ancestry APOL1 low-risk were included as external reference. Baseline covariates include age, sex, eGFR (CKD-EPI 2021), and albumin-to-creatinine ratio (UACR). To better enable comparison between the African ancestry APOL1 high-risk and low-risk groups, propensity score matching was applied using age, sex, eGFR, UACR, diabetes, hypertension, and cardiovascular disease, with separate matching performed for participants with eGFR >60 and ≤60 mL/min/1.73 m^2 (Appendix 1 to 3).

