### **3.7 Statistical Analysis**

The APOL1–high-risk cohort will be randomly divided into an 80% training set and 20% test set (stratified by outcome incidence). In the training set, candidate proteins will be selected via an elastic-net penalized Cox proportional hazards regression (age, sex, baseline eGFR, and log2(UACR) included as unpenalized covariates). Tuning parameters ( $\alpha$ ,  $\lambda$ ) will be chosen by 8-fold cross-validation. The final APRS model will include the nine selected proteins plus the four clinical covariates. Model discrimination will be quantified

by time-dependent AUC (tAUC) at prespecified time points and Harrell's C-index. Model performance will be compared to the KFRE (4-variable equation) and established CKD risk scores.

Proportional hazards assumptions for APRS and covariates will be tested using Schoenfeld residuals. Sensitivity analyses will address potential biases: we will apply inverse-probability-of-censoring weighting (IPCW) to account for informative loss-to-follow-up, computing weights within the training set. Feature stability will be assessed via bootstrap resampling. We will compute net benefit using decision-curve analysis (assuming equal weight for false positives and negatives). To gauge clinical utility, we will calculate the number needed to treat (NNT) to prevent one composite event under a hypothetical APOL1-targeted therapy: assuming a relative risk reduction of 27% (as reported for inaxaplin), NNT will be derived as the reciprocal of the absolute risk reduction. Comparisons of NNT between APRS-based risk stratification and standard models (KFRE) will be reported. All tests will be two-sided with  $\alpha=0.05$ .

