## **2 Background and Rationale**

Chronic kidney disease remains a major global health burden, affecting an estimated 10–15% of the population worldwide. Individuals of African ancestry experience a disproportionately higher incidence of chronic kidney disease and progression to end-stage kidney disease. A key driver of this disparity is the presence of APOL1 high-risk alleles (G1 and G2). Individuals who carry two risk alleles (APOL1-HR genotype) face a significantly elevated risk of chronic kidney disease progression—yet most do not develop kidney disease, highlighting substantial phenotypic heterogeneity.

Although the APOL1 genotype is a well-established driver of kidney disease risk, not all carriers of HR alleles progress to end-stage kidney disease. Large-scale studies have estimated that ~20% of individuals with APOL1-HR may eventually develop kidney failure. Current clinical tools, including the Kidney Failure Risk Equation and other creatinine-based or albuminuria-based formulas, often underperform in predicting kidney outcomes at earlier stages (estimated glomerular filtration rate, eGFR  $\geq 60$  mL/min/1.73m^2). Consequently, there is an urgent need for noninvasive biomarkers that can distinguish individuals at greatest risk, enabling timely interventions (e.g., APOL1 inhibitors, stricter blood pressure control, etc.).

High-throughput proteomics (e.g., SomaScan®, Olink®) has become increasingly accessible for large patient cohorts. Circulating protein levels may reflect underlying pathophysiological mechanisms more directly than genetic risk alone. Our preliminary data in African American patients with APOL1-HR genotypes identified multiple protein signals that correlate with adverse renal outcomes. In this study, we comprehensively assess the utility of these protein markers in a combined protein-clinical model, test their incremental value beyond genetic or clinical risk factors, and validate the model in independent cohorts.

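### The random PMBB split ignores membership of the prior 550-person dataset, so the 171-person test set cannot be shown to be independent of earlier protein-outcome analyses

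*Combined protocol and SAP*

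**What the plan says.** The Summary of the change presents the document as a revision: "This revised protocol expands and refines our original design to improve risk prediction for APOL1-associated kidney disease". Protocol 3.2 gives the growth of the high-risk cohort: "We have identified 1,113 eligible participants for the primary cohort (expanded from 550 in the prior dataset".

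Outcome results were in hand before the revision. Protocol 1 states: "In our preliminary analyses, multiple circulating protein biomarkers were associated with long-term kidney outcomes". SAP 2 says that preliminary data in patients with the high-risk genotype "identified multiple protein signals that correlate with adverse renal outcomes". Neither passage gives a sample size or names the dataset used. Protocol 1 then sets the aim: "We now propose to refine and validate APOL1 Proteomic Risk Score (APRS) for early risk stratification in this population".

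Protocol 3.7 says the high-risk cohort "will be randomly divided into an 80% training set and 20% test set", stratified by outcome incidence; SAP 6.4.1 stratifies on key clinical parameters instead. Neither uses prior-dataset membership, and no other section reports or limits the overlap. Within the same forward-looking plan, Protocol 3.7 already fixes the panel size: "The final APRS model will include the nine selected proteins plus the four clinical covariates".

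SAP 3 puts the derivation set at 851 and lists 262 high-risk participants with CKD as a secondary set. Supplementary Table 1 shows the realised split: 680 training and 171 test, with 121 and 32 composite events.

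**The concern.** A held-out set supports a validation claim only if its outcomes played no part in building the model. Suppose anything was carried over from the preliminary analyses: candidate proteins, panel size, covariates or operating points. Those choices would then rest partly on outcomes of people whom a fresh random split can return to the test set. Confining protein selection to the new training set would not cure this.

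Some wording suggests that results already existed when the plan was written. The number of proteins is fixed before the described selection. SAP 8.2 uses an apparent performance of 0.88 as its own value, without giving a source. SAP 6.5 refers to an operating point used in the revision. None of this proves carry-over, but no statement excludes it.

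What is at stake is optimism in the PMBB test-set C-index and time-dependent AUC.

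**Working it through.** The documents give no figure for the overlap, so it has to be bounded.

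**Inputs**
- High-risk cohort 1,113, of which 550 were in the prior dataset (Protocol 3.2).
- Split set 851; CKD set 262 (SAP 3; Appendices 1 and 2).
- Test set 171 with 32 events (Supplementary Table 1).
- Assumption: all 550 are still within the 1,113.

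**The plan's own counts.** 851 + 262 = 1,113; 680 + 171 = 851; 171/851 = 20.1%. These agree. The set that is split is 851, so 550/1,113 = 49.4% is not the relevant share.

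**Bounds on prior participants among the 851.** Between 0 and 262 of the 550 could be in the CKD set.
- Lower bound: 550 − 262 = 288, and 288/851 = 33.8%.
- Upper bound: 550/851 = 64.6%.
- Same eGFR mix as the whole 1,113: 550 × 851/1,113 ≈ 421, or 49.5%.

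**Expected overlap in a random test set of 171.** Expected prior participants = 171 × x/851. Expected prior events = 32 × x/851, which assumes that prior and new participants have the same event rate. The 95% range is hypergeometric.

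| Prior participants in the 851 (x) | Expected in test set (95% range) | Share | Expected events of 32 | New participants in test set |
|---|---|---|---|---|
| 288 | 58 (47–69) | 34% | 11 | 113 |
| 421 | 85 (73–96) | 49% | 16 | 86 |
| 550 | 111 (99–121) | 65% | 21 | 60 |

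**Could the test set be drawn from new participants alone?** New participants in the 851 number 851 − 550 = 301 to 851 − 288 = 563. Both exceed 171. Training would stay at 851 − 171 = 680: all 288 to 550 prior participants plus 392 to 130 new ones.

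**Precision if only the new part of the present test set is reported.** This uses the Hanley–McNeil standard error at an assumed AUC A = 0.80, ignoring censoring. With n1 events and n0 non-events, Q1 = A/(2 − A) = 0.667 and Q2 = 2A²/(1 + A) = 0.711. The variance is [A(1 − A) + (n1 − 1)(Q1 − A²) + (n0 − 1)(Q2 − A²)]/(n1·n0).
- 86 people, 16 events: SE = 0.070, 95% half-width ±0.14.
- 60 people, 11 events: ±0.17.
- 113 people, 21 events: ±0.12.
- Full 171 with 32 events, for comparison: ±0.10.

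**The case against.** The strongest reply is that carry-over is not shown. SAP 6.4.2 describes selection from the top 20% of proteins by univariate AUC, over about one million combinations, and does not restrict it to proteins found earlier. The mention of nine proteins may simply be text updated after the current selection: SAP 6.4.3 reports that selection in the past tense, and Supplementary Table 2 marks nine proteins as included. Use of the 550 in the preliminary analyses is also an inference. All of this stands. It makes the bias uncertain in size and possibly nil, but it does not make the test set demonstrably independent.

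Three stronger readings are tempting and should be resisted.

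- **That half of the test set has certainly been analysed before.** That share takes 1,113 as the denominator, or assumes the same eGFR mix among prior and new participants. SAP 4.2 reports higher eGFR in the second assay run but does not link runs to the prior and new datasets.
- **That pooled testing at 0.05 is a second look needing alpha spending.** The plan describes no claim at a first analysis, no stopping rule and no confirmatory test of that kind. SAP 6.2 applies Benjamini–Hochberg control to univariate protein tests. That does not correct for an earlier analysis, but the score is judged mainly on C-index and time-dependent AUC, so optimism is the relevant harm.
- **That the panel could be noise picked from the prior data.** Supplementary Table 2 speaks against this: WFDC2 (3.54, 2.98–4.22), MMP7 (1.10, 1.06–1.14) and CILP2 (0.57, 0.50–0.64) are also associated with outcome in CRIC.

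Two further points stand. External validation in ARIC and UK Biobank is planned and is not touched by this overlap. And SAP 6.4.3 chooses the model by deviance within the testing set, so new test participants are not clean either while that rule remains.

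**Conclusion.** The point holds in a limited form. Earlier protein-outcome results existed, the cohort was enlarged from a prior dataset, and the split takes no account of prior membership. If all 550 are within the 1,113, an estimated 34–65% of the 171 test participants come from that dataset. That is about 58 to 111 people and, at equal event rates, about 11 to 21 of the 32 events.

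Two links are inferred: that the preliminary analyses used the 550, and that something from them shaped the present score. If nothing was carried forward, this overlap causes no bias, and the documents do not allow its size to be estimated otherwise. The damage is confined to the PMBB internal validation. The change is worth making because it is cheap and can keep the test set at its present size.

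**What to change.** In Protocol 3.7 and SAP 6.4.1:

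1. Add a prior-dataset flag and report membership by training and test set. State which participants the preliminary analyses used and what, if anything, was carried forward.
2. Preferred: keep all prior participants in training and draw the 171-person test set from the newly added participants. At minimum, keep the present split, report C-index and time-dependent AUC separately for prior and new test participants, and base the internal-validation claim on the new ones.
3. In SAP 6.4.3, remove model choice within the testing set and confine it to cross-validation in the training set. Without this, item 2 does not give a clean internal validation.
4. Name ARIC and UK Biobank as the confirmatory validation.

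Protocol 3.2, which calls 1,113 participants eligible under eGFR above 60, should also be reconciled with the 851 and 262 in SAP 3.

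The cost is a flag and a re-run. A test set of new participants only may reflect one assay run's eGFR mix, which should be described alongside the result. The minimum option widens the intervals, to about ±0.14 for an assumed AUC of 0.80 with 16 events.
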